#### Analysis of secondary outcomes

Secondary outcomes, such as the other dimensions of the SF-36, EQ-5D-3L, BRS, GSE, de Jong Gierveld Loneliness Scale at six months’ follow-up, will be compared between the intervention and control arm using a multi-level mixed effects linear regression model with baseline score as a covariate. A 95% CI for the mean difference in this parameter between the treatment groups will also be calculated. Participants will be followed up at 24 months post randomisation. Mean SF-36 (MH), other SF-36 dimensions, BRS, GSE, PHQ-9, EQ-5D-3L, de Jong Gierveld Loneliness Scale dimension scores at 24 months’ follow-up will be compared again using multi-level mixed effects linear regression model with baseline score as a covariate. A 95% CI for the mean difference in this parameter between the treatment groups will also be calculated.

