#### Aims and objectives

The primary aim of the study is to identify how mental wellbeing, self-efficacy and resilience can be supported in people aged 65 years or older by:

1. Evaluating the clinical and cost effectiveness of a psycho-social intervention to promote healthy ageing (Lifestyle Matters) compared to usual care.

2. Examining the nature of the underlying mechanisms that might promote self-efficacy and resilience.

3. Determining the long term sustainability of the intervention and any associated treatment effects.

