All six month follow-ups will be completed face-to-face with participants by a blinded assessor. It is anticipated that due to the nature of the intervention that participants, although asked not to reveal the study arm allocation, may inadvertently unblind assessors. Any knowledge of study arm allocation for each participant will, therefore, be recorded at 6 and 24 month follow-up by the blinded assessor. At 24 month follow-up the blinded assessor will deliver and complete the Assessor Booklet by telephone. The Participant Booklet will be sent by post to the participant for self-completion, including a return pre-paid envelope. Assistance will be provided to participants where a need is identified, for example, large print versions of questionnaires, telephone assistance or a home visit.

Due to the length of time between baseline and final assessment, a significant risk will be the potential for deterioration in general health and, in particular, cognitive capacity for some participants. If the accommodation needs of a participant have changed during this time, for example, a need to enter a residential home, this will not prevent follow-up; however, a move to a nursing home will be managed on a case by case basis. Although there is no intention to conduct the 6 Item Cognitive Impairment Test with participants before the 24 month follow-up, the 6CIT may be repeated to record any changes in cognitive function.

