### Statistical analysis

As the trial is a pragmatic parallel group randomised with a usual (control) treatment arm, data will be reported and presented according to a revised CONSORT statement [37]. Statistical analysis will be performed on an intention-to-treat-basis. All exploratory tests will be two-tailed with alpha = 0.05. Baseline demographic (for example, age, gender, number and proportion of sample who are couples) and health related quality of life data (SF-36) will be assessed for comparability between groups. The outcome data to be collected are hierarchical or multi-level in nature with individual participants nested or clustered within couples; who are nested or clustered within the Lifestyle Matters facilitation group who are then nested within a treatment group. The statistical analysis, of the outcome data, will take into account the hierarchical or clustered nature of the data by using a multi-level mixed effects linear regression model. Mixed effects models are characterised by containing both fixed and random effects. We shall assume a fixed effect for the randomised treatment group but random effects for the couple and Lifestyle Matters facilitation group. Individual participants who are not part of a couple will be treated as clusters of size one; similarly, participants randomised to the control usual care group will be treated as clusters of size one (or two if they are a couple).

To avoid bias, the independent Trial Steering Committee (TSC), the study statisticians, health economists and the research assistants collecting data at 6 and 24 months will be blinded to treatment allocation whilst the trial is ongoing. To remain blinded, assessors will not be made aware of participants’ allocation in the study and participants will be asked not to inform the assessor whether they took part in the groups when visited at 6 and 24 month follow-up. The Trial Manager, Chief Investigator, Principal Investigators, Fidelity assessment Lead, Trial Support Officer and participants will not be blinded.

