#### Analysis of primary outcome

The primary analysis will compare mean SF-36 Mental Health dimension (MH) scores at six months post randomisation between the intervention group and control arms using a random-effects or multi-level mixed effects linear regression model to allow for the clustering of the outcomes within couples and Lifestyle Matters facilitation groups with baseline MH score as a covariate [38,39]. A 95% confidence interval (CI) for the mean difference SF-36 mental health dimension scores between the intervention and control arms will also be calculated. For the primary outcome, the SF-36 MH score at six months follow-up, missing data will be imputed using multiple imputations with age, gender and baseline MH scores as predictors.

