A potentially important benefit of the intervention is that it may result in important cost savings to the NHS. The use of services by trial participants will be collected in detail using a Health and Social Care Service Use Questionnaire that will be administered by telephone or face to face. Interviewer administration is essential in order to obtain accurate and useable data on the use of all NHS and Personal and Social Services. Service use will be costed using most recent National Reference Cost Data and Unit Costs of Health and Social Care [42,43]. Missing data will be dealt with using multiple imputation for SF-6D and resource use data [44]. The central analysis of mean incremental costs per QALY will be subjected to a full sensitivity analysis of key parameters including the measure used to estimate QALYs and number participants at the weekly sessions. A full probabilistic sensitivity analysis will be performed to examine the probability of cost effectiveness of the intervention for the NHS for different levels of costs and QALY gains [45]. There will also be a supplementary cost consequences analysis that will include the other outcome measures [40].

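### As written, the 24-month comparison ignores the six-month score and has no imputation, so it assumes more about missing data than the collected data require

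*Protocol article*

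**What the plan says.** All of this is in the protocol article.

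- **24-month model (Analysis of secondary outcomes).** Scores at 24 months' "follow-up will be compared again using multi-level mixed effects linear regression model with baseline score as a covariate". The baseline score is the only covariate named.
- **Random effects (Statistical analysis).** "We shall assume a fixed effect for the randomised treatment group but random effects for the couple and Lifestyle Matters facilitation group". No participant-level term links a person's 6- and 24-month scores, so this is a single-time-point model.
- **Imputation of clinical outcomes (Analysis of primary outcome).** "For the primary outcome, the SF-36 MH score at six months follow-up, missing data will be imputed", with age, gender and baseline MH as predictors. No other clinical outcome or time point is mentioned.
- **Imputation in the economic evaluation (Cost effectiveness analysis).** "Missing data will be dealt with using multiple imputation for SF-6D and resource use data". The SF-6D is derived there from the SF-36 at baseline, 6 and 24 months.
- **Analysis set (Statistical analysis).** "Statistical analysis will be performed on an intention-to-treat-basis".
- **Risk by the final assessment (Outcome measures).** "a significant risk will be the potential for deterioration in general health and, in particular, cognitive capacity for some participants". The same section says that a move to a residential home does not end follow-up, and it offers large print, telephone help or a home visit.
- **Aim 3 (Aims and objectives).** "Determining the long term sustainability of the intervention and any associated treatment effects".

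**The concern.** A single-time-point mixed model takes no information from a person whose 24-month score is missing. With only arm and baseline in the model, it is unbiased if, given those two, loss is unrelated to how the person was doing later. The six-month score says something about exactly that. It is collected in both arms, but the stated 24-month model does not use it.

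The document also treats the same instrument in two ways. The SF-6D, which comes from the SF-36, is multiply imputed for the economic result, while no method is stated for a missing 24-month SF-36 score in the clinical result.

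At stake is the main quantitative test of sustainability, one of three stated aims. If people doing poorly at six months leave more often from one arm, those still observed at 24 months are no longer comparable between arms, even after baseline adjustment.

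**Working it through.** **1. The plan's own figure.** Inputs from Sample size: difference 8, SD 20, 80% power, two-sided 5%, cluster size 10, intra-cluster correlation 0.01, 20% loss.

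- n per arm = 2 × (1.960 + 0.842)² × 20² / 8² = 98.1, so 99.
- Design effect = 1 + (10 − 1) × 0.01 = 1.09; 98.1 × 1.09 = 106.9, so 107.
- 107 / 0.8 = 133.75, so 134.

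The stated 99, 107 and 134 are reproduced. The document gives no bias figure for 24 months, so the rest rests on assumptions.

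**2. Scale.** With 107 analysed per arm and an assumed baseline-to-24-month correlation of 0.5, the standard error of the 24-month difference is 20 × √(1 − 0.5²) × √(2 × 1.09 / 107) = 17.32 × 0.1427 = 2.47.

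**3. Simulation set-up.** Each scenario had 1,000,000 participants, half per arm, with no clustering. MH at 0, 6 and 24 months was trivariate normal with mean 68.3 (the survey mean in Sample size) and SD 20. Everyone had a six-month score. Loss at 24 months followed logit P(loss) = a − s × (six-month score − 68.3)/20. Two estimators were compared: regression of observed 24-month scores on arm and baseline, and an analysis that also uses the six-month score (regression within arm, standardised to all randomised). The correlations, loss rates by arm and s are assumed; none is in the document.

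**4. One loss rule for both arms** (same a and s). Correlations were 0.7 (0 to 6 months), 0.6 (0 to 24) and 0.7 (6 to 24), with average loss about 30%.

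- No treatment effect: bias 0.02 to 0.05, which is simulation noise.
- 8-point effect at six months: about −0.1 at s = 0.5, −0.30 to −0.34 at s = 1, and −0.52 to −0.61 at s = 1.5.

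**5. Loss that differs by arm.** Correlations were 0.6 (0 to 6) and 0.5 (0 to 24). The effect was 8 points at 6 months and 4 at 24, with s = 1 where loss depends on the score. The last three columns give the bias of the baseline-only analysis by 6-to-24-month correlation.

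| Loss, control / intervention | Loss depends on six-month score in | 0.6 | 0.7 | 0.8 |
|---|---|---|---|---|
| 20% / 20% | both arms | 0.01 | 0.01 | 0.03 |
| 25% / 15% | both arms | −0.48 | −0.65 | −0.89 |
| 30% / 20% | both arms | −0.47 | −0.68 | −0.84 |
| 30% / 15% | both arms | −0.75 | −0.97 | −1.31 |
| 40% / 20% | both arms | −0.96 | −1.27 | −1.65 |
| 20% / 20% | control only | −1.06 | −1.37 | −1.75 |
| 30% / 30% | control only | −1.58 | −2.15 | −2.53 |

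With the six-month score used, the bias is within 0.08 of zero in every row. Negative values understate the intervention; if the selective loss were in the intervention arm instead, the sign would turn.

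**6. Consistency check.** The bias should be about β times the between-arm difference in how far the retained participants' baseline-adjusted six-month scores have shifted. Here β = (r₆,₂₄ − r₀,₆ × r₀,₂₄) / (1 − r₀,₆²).

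- β = (0.6 − 0.30)/0.64 = 0.469 for a 6-to-24-month correlation of 0.6; likewise 0.625 for 0.7 and 0.781 for 0.8.
- Row 20% / 20%, control only: 1.06/0.469 = 2.26, 1.37/0.625 = 2.19, 1.75/0.781 = 2.24.

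The implied shift is about 2.2 points each time, as it should be, since the loss mechanism is the same across that row.

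**7. Against the standard error.** 0.6/2.47 = 0.24, 1.3/2.47 = 0.53 and 2.5/2.47 = 1.01 standard errors.

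**The case against.** **The article does not say that only people with a 24-month score are analysed.** True. That follows from the stated model, and the separate analysis plan, not shown, may add imputation or sensitivity analyses. This limits the point to what the article fixes. But the article does fix a model and its covariate, and the analysis plan would have to change or supplement that model to bring in the six-month score.

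**A reader might infer that the plan expects selective loss.** It does not say so. Outcome measures names deterioration as a risk and then sets out ways to keep following such participants; the article adds newsletters and a prize draw to hold people in the trial. Selective loss is plausible, no more.

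**A reader might infer that the bias exceeds a point.** The natural case, one loss rule acting in both arms, gives 0 to 0.6 point. Passing one point takes one-arm dependence, or clearly unequal loss rates with a strong 6-to-24-month correlation. The document supports neither; Sample size gives a single 20% loss figure. Even 2.5 points is below the 5 to 10 points that the article treats as relevant.

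**The remedy does not reach all deterioration.** This stands. Someone well at six months who declines later and is lost is not identified by the six-month score, and those lost before six months gain nothing. The near-zero bias in the simulation follows from making loss depend on the observed six-month score.

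**Precision gains are small.** Also true: in a simulation with 134 per arm and about 25% missing, the standard error fell from 2.48 to 2.40, a drop of 0.08/2.48 = 3%.

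**Conclusion.** The point holds in limited form. As written, the 24-month comparison adjusts for baseline only, no stated imputation reaches it, and the collected six-month score goes unused. It therefore rests on a stronger missing-data assumption than it needs to.

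The size is conditional on assumed correlations and loss patterns: about 0 to 0.6 point with one loss rule in both arms, about 0.5 to 1.3 points when loss rates differ by 10 to 15 percentage points, and about 1.0 to 2.5 points when loss depends on a low six-month score in one arm only. The standard error is about 2.5. The documents do not show that the 24-month result will be biased, nor by how much.

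This is an inexpensive improvement to the main quantitative test of aim 3. It concerns a secondary time point.

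**What to change.** For each outcome measured at both times, estimate the 24-month difference in one of two ways:

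- fit one longitudinal mixed model to the 6- and 24-month scores together, with arm × time, baseline × time, the same couple and facilitation-group random effects, and correlated within-person residuals; or
- multiply impute the 24-month scores separately by arm, with the six-month score among the predictors, and keep the stated 24-month model.

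State alongside it that either approach removes bias only where loss depends on observed scores, and does not deal with loss through unobserved later decline or death.

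The cost is analysis-plan wording and slightly more complex modelling. No new data are needed.

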### Cost effectiveness analysis

A trial based economic evaluation will be undertaken of an intention-to-treat comparison of the costs and outcomes of the two trial arms. A cost effectiveness analysis will be undertaken of the incremental cost per QALYs of the Lifestyle Matters intervention compared with treatment as usual [40]. QALYs will be calculated using the SF-6D preference-based index derived from the SF-36 administered at baseline, 6 and 24 months [41]. The QALY gain from the intervention will be estimated using a standard area under the curve calculation. A sensitivity analysis will be undertaken using utility values from the EQ-5D, also collected in the trial [27]. The total cost consequences of the intervention will be estimated at the individual participant level and will include the costs of providing the four month Lifestyle Matters intervention and the subsequent consequences for the use of routine health and social care services. A detailed costing of the weekly facilitated sessions will be undertaken, including recruitment (though postal invitation), administration, hire of local community venues, facilitator salaries, refreshments participant travel if required and any materials used. Care will be undertaken to exclude all research costs. Resources will be costed using local price data to estimate a total cost per session. The number of participants attending each session will be recorded and an average level of capacity used to estimate an average cost per attendance. Finally, this estimate will be applied to the actual number of sessions each participant attended.

A potentially important benefit of the intervention is that it may result in important cost savings to the NHS. The use of services by trial participants will be collected in detail using a Health and Social Care Service Use Questionnaire that will be administered by telephone or face to face. Interviewer administration is essential in order to obtain accurate and useable data on the use of all NHS and Personal and Social Services. Service use will be costed using most recent National Reference Cost Data and Unit Costs of Health and Social Care [42,43]. Missing data will be dealt with using multiple imputation for SF-6D and resource use data [44]. The central analysis of mean incremental costs per QALY will be subjected to a full sensitivity analysis of key parameters including the measure used to estimate QALYs and number participants at the weekly sessions. A full probabilistic sensitivity analysis will be performed to examine the probability of cost effectiveness of the intervention for the NHS for different levels of costs and QALY gains [45]. There will also be a supplementary cost consequences analysis that will include the other outcome measures [40].

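### The QALY gain is tied to a plain area-under-the-curve calculation with no stated adjustment for baseline utility, although the clinical outcomes are baseline-adjusted

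*Protocol article*

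**What the plan says.** In the protocol article, the section on cost effectiveness analysis sets up the economic comparison: "A trial based economic evaluation will be undertaken of an intention-to-treat comparison of the costs and outcomes of the two trial arms". It then says how utilities enter: "QALYs will be calculated using the SF-6D preference-based index derived from the SF-36 administered at baseline, 6 and 24 months". The next sentence gives the effect measure: "The QALY gain from the intervention will be estimated using a standard area under the curve calculation". EQ-5D utilities are to replace the SF-6D in a sensitivity analysis.

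No regression model or baseline covariate is named for QALYs. The planned sensitivity work is described as a "full sensitivity analysis of key parameters including the measure used to estimate QALYs and number participants at the weekly sessions", followed by a probabilistic analysis; baseline adjustment is not among the items named.

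The clinical analyses are more specific. The primary SF-36 Mental Health comparison is made "with baseline MH score as a covariate". The secondary outcomes, which include the other SF-36 dimensions and the EQ-5D-3L, are compared "using a multi-level mixed effects linear regression model with baseline score as a covariate". Randomisation is stratified by site only, so baseline utility is not balanced by design.

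**The concern.** The SF-36 and EQ-5D responses are adjusted for baseline when analysed as clinical outcomes. When the same responses are turned into QALYs, no adjustment is stated. The sentence on the QALY gain describes the effect of the intervention, not only a participant's score, so an analyst who follows it literally would subtract one arm's mean area from the other's.

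The baseline utility is itself part of each participant's area, and it usually predicts the later utilities. A chance difference between arms at baseline then enters the incremental QALY twice: once through its own weight, and again through its persistence at 6 and 24 months. The incremental QALY is the denominator of the cost per QALY, and its uncertainty feeds the probability of cost-effectiveness. At stake are an avoidable conditional shift and avoidable variance in the main economic result.

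**Working it through.** **Inputs from the article.** Utilities are measured at 0, 6 and 24 months, that is 0, 0.5 and 2 years. The sample size is 107 per arm after the design effect and 134 per arm randomised.

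**Inputs assumed.** Equal variance of utility at the three times, one common correlation r of 0.4 to 0.7, linear interpolation, no discounting, and clustering ignored. The article gives neither r nor an SF-6D standard deviation.

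**The plan's own figures.** The article states no QALY figure to reproduce. Its sample size does reproduce: 2 × (1.96 + 0.8416)² × 20² / 8² = 98.1, rounded up to 99; design effect 1 + 9 × 0.01 = 1.09; 99 × 1.09 = 107.9, stated as 107; 107 / 0.8 = 133.75, rounded up to 134. It was powered on the SF-36 Mental Health score and is not affected by this point.

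**Step 1: weights in the area under the curve.**
- 0 to 0.5 years: 0.5 × (u0 + u6) / 2 = 0.25·u0 + 0.25·u6
- 0.5 to 2 years: 1.5 × (u6 + u24) / 2 = 0.75·u6 + 0.75·u24
- QALY = 0.25·u0 + 1.00·u6 + 0.75·u24

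The weights sum to 2 years, and baseline carries 0.25 / 2 = 12.5% of the total.

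**Step 2: how far a baseline difference d carries through.** The slope of the QALY on u0 is 0.25 + r × (1.00 + 0.75) = 0.25 + 1.75r. The first term is the direct part.

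**Step 3: precision.** In units of the utility variance, Var(QALY) = 0.25² + 1.00² + 0.75² + 2r × (0.25 × 1.00 + 0.25 × 0.75 + 1.00 × 0.75) = 1.625 + 2.375r. The share explained by baseline is R² = (0.25 + 1.75r)² / (1.625 + 2.375r). The ratio of adjusted to unadjusted standard error is √(1 − R²).

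| r | Total shift per unit d | Var(QALY) | R² | SE ratio | SE reduction |
|---|---|---|---|---|---|
| 0.4 | 0.95 | 2.575 | 0.35 | 0.81 | 19% |
| 0.5 | 1.125 | 2.8125 | 0.45 | 0.74 | 26% |
| 0.6 | 1.30 | 3.05 | 0.55 | 0.67 | 33% |
| 0.7 | 1.475 | 3.2875 | 0.66 | 0.58 | 42% |

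The percentages do not depend on the standard deviation. Widening r to 0.3 and 0.8 gives SE ratios of 0.86 and 0.48, so the direction is the same throughout.

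**Step 4: an illustration in QALYs.** Assume an SF-6D standard deviation of 0.12.
- With 107 per arm, the standard error of the chance baseline difference is 0.12 × √(2/107) = 0.0164. An imbalance of one standard error moves the unadjusted incremental QALY by 0.95 × 0.0164 = 0.016 to 1.475 × 0.0164 = 0.024.
- With all 134 per arm, which fits an intention-to-treat comparison with imputed SF-6D, it is 0.12 × √(2/134) = 0.0147, and the shift is 0.014 to 0.022.

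These amounts scale in proportion to the assumed standard deviation. For a range of 0.10 to 0.14, multiply by 0.83 to 1.17.

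**The case against.** The strongest reply is that silence is not a decision. An area under the curve is how a participant's QALY is built, and it is fully compatible with a later regression on baseline utility; the remedy proposed here keeps it. A journal article condenses the full plan, the economic section names no between-arm model at all, and baseline-adjusted clinical models suggest no wish to ignore baseline values. This largely stands. A reader might infer that the trial has chosen an unadjusted QALY comparison, or that the article contradicts itself. The article says neither: the economic section is less specific than the clinical ones. What survives is narrower. The published sentence attaches the area-under-the-curve calculation to the gain from the intervention, and so names an estimator for the treatment effect without the covariate used elsewhere.

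Two further inferences are not supported.
- That the QALY result will be biased. Randomisation makes the unadjusted comparison unbiased on average; the cost is a shift conditional on the imbalance that occurs, plus extra variance.
- That chance imbalance could be as large as a plausible QALY gain. The article gives no expected gain to compare it with.

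It is also fair to object that site terms and random effects for the QALY model would be separate specification choices. They are not part of this point.

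**Conclusion.** The point holds as a modest one. Followed as written, the QALY sentence yields an incremental QALY that carries chance baseline imbalance and is less precise than the data allow. The direct part of the shift, 0.25d, follows from the visit times and linear interpolation alone. The total of about 0.95d to 1.475d and the forgone standard-error reduction of about 19% to 42% rest on equal variances and a common correlation of 0.4 to 0.7, which the article does not supply. The figures in QALYs are illustrations only. An economic analysis plan that is not shown may already contain the adjustment, in which case the article's sentence only needs to match it.

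**What to change.** Keep the area under the curve to construct each participant's QALY. State that the incremental QALY will be estimated by regressing that QALY on treatment arm and the matching baseline utility: baseline SF-6D for the base case and baseline EQ-5D for the sensitivity analysis. State also that this adjusted estimate and its uncertainty are carried into the cost per QALY and the probabilistic sensitivity analysis.

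Both instruments are already collected at baseline, so the change costs a sentence or two in the economic analysis plan. It needs no new data, no extra participants and no change to the trial's conduct.
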